## Abstract

**Background::**

Lower respiratory tract infections like acute bronchitis, exacerbated chronic obstructive pulmonary disease and community-acquired pneumonia are often unnecessarily treated with antibiotics, mainly because of physicians' difficulties to distinguish viral from bacterial cause and to estimate disease-severity. The goal of this trial is to compare medical outcomes, use of antibiotics and hospital resources in a strategy based on enforced evidence-based guidelines versus procalcitonin guided antibiotic therapy in patients with lower respiratory tract infections.

**Methods and design::**

We describe a prospective randomized controlled non-inferiority trial with an open intervention. We aim to randomize over a fixed recruitment period of 18 months a minimal number of 1002 patients from 6 hospitals in Switzerland. Patients must be >18 years of age with a lower respiratory tract infections <28 days of duration. Patients with no informed consent, not fluent in German, a previous hospital stay within 14 days, severe immunosuppression or chronic infection, intravenous drug use or a terminal condition are excluded. Randomization to either guidelines-enforced management or procalcitonin-guided antibiotic therapy is stratified by centre and type of lower respiratory tract infections. During hospitalization, all patients are reassessed at days 3, 5, 7 and at the day of discharge. After 30 and 180 days, structured phone interviews by blinded medical students are conducted. Depending on the randomization allocation, initiation and discontinuation of antibiotics is encouraged or discouraged based on evidence-based guidelines or procalcitonin cut off ranges, respectively. The primary endpoint is the risk of combined disease-specific failure after 30 days. Secondary outcomes are antibiotic exposure, side effects from antibiotics, rate and duration of hospitalization, time to clinical stability, disease activity scores and cost effectiveness. The study hypothesis is that procalcitonin-guidance is non-inferior (i.e., at worst a 7.5% higher combined failure rate) to the management with enforced guidelines, but is associated with a reduced total antibiotic use and length of hospital stay.

**Discussion::**

Use of and prolonged exposure to antibiotics in lower respiratory tract infections is high. The proposed trial investigates whether procalcitonin-guidance may safely reduce antibiotic consumption along with reductions in hospitalization costs and antibiotic resistance. It will additionally generate insights for improved prognostic assessment of patients with lower respiratory tract infections.

**Trial registration::**

ISRCTN95122877

## Background

Lower respiratory tract infections (LRTI) including acute bronchitis, acute exacerbations of chronic obstructive pulmonary disease (AECOPD) and community-acquired pneumonia (CAP), account for almost 10% of the worldwide burden of morbidity and mortality, and thus, importantly contribute to antibiotic overuse and allocation of health resources [1,2]. Although most LRTI are of viral origin, approximately 75% of antibiotics are prescribed because viral etiology and disease severity are difficult to recognize with traditional clinical and laboratory means [2]. Current criteria for assessing the severity of CAP, such as the pneumonia severity index (PSI) and the CAP severity on presentation to hospital scale (CURB65) are well validated, but have important drawbacks for routine care [3-6]. They only predict mortality in CAP and depend mainly on age, thereby underestimating the disease-related morbidity in younger patients. Furthermore, they dichotomize continuously measured values (e.g. respiratory rate) into normal and abnormal values and show a high intra-observer variation of around 10 percent.

A widely used approach to estimate the probability of a bacterial origin and the disease severity of a LRTI is the use of the C-reactive protein. However, this biomarker lacks sensitivity and specificity, and thorough studies about its effect on antibiotic use are lacking [7,8]. More promising appears to be the level of circulating procalcitonin (PCT) which has been demonstrated to correlate with the likelihood for a bacterial infection [7,9]. We conceived and successfully validated PCT guided diagnosis using cut-off ranges in the continuum of LRTI in four intervention trials by randomizing patients to PCT guided antibiotic prescription versus standard care and monitored clinical outcome. In these trials we circumvented the gold standard dilemma for the etiologic diagnosis of LRTIs by assuming absence of serious bacterial infection in patients recovering without antibiotics [10-14].

Some limitations of the previous intervention trials need to be considered. Three of the four trials were conducted at a single University Hospital, limiting the external validity of this approach [11,12,14]. Routine use of guidelines for antibiotic prescriptions was only partly enforced in the standard care group [11-14]. Only the primary care trial had adequate power to show non-inferiority in days with restrictions from LRTI by PCT guidance. However, the trial was not designed to show non-inferiority from severe infectious disease complications, more typically seen in hospitalized patients with higher complication rates. Finally, despite a marked reduction of the duration of antibiotic therapy by PCT guidance, the length of hospital stay was not reduced since it was not a target of intervention in all previous trials.

The aim of the proposed "ProHOSP"-study is to address these limitations from the previous trials and to study additional diagnostic and prognostic biomarkers for the management of LRTIs. In addition this trial shall assess the impact of a biomarker driven LRTI management on hospital stay and costs.

## Methods

The objectives of this randomized controlled, open intervention trial are to evaluate whether a PCT guided diagnostic and therapeutic strategy in patients with LRTI lead to similar patient relevant outcomes, reduced total antibiotic use as well as length of hospitalization as compared to a management without PCT testing but based on the enforced implementation of current guidelines. The primary study hypothesis is that a PCT guided LRTI management is non-inferior to standard care based on implemented guidelines. The primary endpoint is disease specific failure within 30 days following index hospital admission and we assume non-inferiority if the combined disease specific failure rate is less than 7.5%.

Patients from six hospitals in Switzerland are being included. Full ethical approval for this trial which is in compliance with the Helsinki Declaration has been obtained from all local ethical committees. All responsible heads of the medical departments of the participating study hospitals have approved and signed the study protocol and all participating patients must give written informed consent.

This trial is supervised by an independent safety monitoring board which is not involved in the design and the conduct of the trial. The board consists of a pneumologist, an infectious disease specialist and an intensive care specialist.

### Setting

We recruit the patients in six secondary and tertiary care clinics in northern and central Switzerland. The characterisation of the study clinics is presented in table 1. The 6 public hospitals are variable in size, patient care capacity and employment of medical and nursing staff, but have a comparable length of hospital stay per patient (mean hospital stay 8.3 +/- 0.57 days)[15].

**Table 1 T1:** Baseline characteristics of the six participating study hospitals in the northern and central part of Switzerland [15].

**Baseline characteristics of the study hospitals**						
	**Universitäts-spital Basel**	**Kantonsspital Liestal**	**Kantonsspital Luzern**	**Kantonsspital Aarau**	**Bürgerspital Solothurn**	**Kantonsspital Münsterlingen**

Status	Public	Public	Public	Public	Public	Public

Number of beds	694	371	616	539	254	252
Mean length of stay (days)	8.5	9.9	8.5	8.5	9.3	8.3
% of private medical coverage*	28.3	19.0	18.9	18.5	25.1	15
Medical staff**	849	125	414	376	97	350
Nursing staff**	1047	315	1074	979	417	414

*Average of medical and surgical patients

** All personal for the care of medical and surgical patients

Local investigators and their staff received a structured seminar to become familiar with the details of the protocol, the rationale and the design of the trial, the study website for patients inclusion and randomisation and all study forms.

In December 2006, all participating hospitals started to consecutively screen all adult patients admitted to the emergency department with suspected LRTI.

### Participants

Inclusion criteria for patients are written informed consent, age ≥ 18 years and admittance from the community or a nursing home with the main diagnosis of acute LRTI (i.e., less than 28 days). LRTI is defined by at least one respiratory symptom (cough, sputum production, dyspnea, tachypnea pleuritic pain) plus one auscultatory finding or sign of infection (core body temperature >38.0°C, shivers, leucocyte count >10 G/L or <4 G/L cells) independent of antibiotic pre-treatment. The LRTI conditions are defined as follows: CAP is defined as a new or increased infiltrate on chest radiograph [16,17]. COPD is defined by post-bronchodilator spirometric criteria according to the GOLD-guidelines as a FEV1/FVC ratio below 70% and the severity categorized according to GOLD criteria [18,19]. Acute bronchitis is defined as LRTI in the absence of an underlying lung disease or focal chest signs or infiltrates on chest X-ray, respectively [20]. Exclusion criteria are the inability to give written informed consent, insufficient German language skills, active intravenous drug users, severe immunosuppression, accompanying chronic infection or endocarditis or very severe medical co-morbidity where death is imminent.

### Intervention

Clinicians in the emergency departments of participating clinics are advised to access a web based study algorithm and enter baseline data of all eligible patients with LRTI on admission and to check all inclusion and exclusion criteria prior to randomisation (figure 1). Randomization of patients to PCT guidance or guideline enforced antibiotic therapy is based on a pre-specified computer generated randomization list and concealed by using a centralized password-secured website [21]. This website provides all study-related information including guidelines and patient flow. The randomization is stratified by the participating clinic and the type of LRTI (acute bronchitis, AECOPD, CAP).

**Figure 1 F1:**
[figure not shown]
All consecutive patients with lower respiratory tract infection are potentially eligible for this trial. If all inclusion criteria are fulfilled and no exclusion criteria are present, the physician has to explain to the patient the trial, ask for participation and get informed consent. After inclusion, the patient is randomized by a web based computerized random allocation algorithm to either the guidelines group or the PCT group, respectively. *CAP *denotes community-acquired pneumonia, *AECOPD *acute exacerbation of chronic pulmonary disease, *AB *antibiotics, *PCT *procalcitonin.

We summarized guidelines on the management of CAP, acute bronchitis and AECOPD based on the most recent guidelines by the European Respiratory Society (ERS) and the American Thoracic Society (ATS) supplemented by evidence from recent guidelines and published current concepts [16,17,19,20]. These guidelines have been adapted by a panel of local internists, emergency physicians, pneumologists, infectious disease experts and clinical epidemiologists and have been successfully used in the clinical setting. To optimize the implementation of these guidelines for all patients the treating physician is enforced to follow web-based guideline algorithms, controlled by email alerts released for every patient screened and recruited, respectively. If the algorithm for PCT guidance or the guidelines for antibiotic therapy are overruled, the study centre has to be informed as soon as possible.

PCT is measured using a rapid sensitive immunoassay with a functional assay sensitivity of 0.06 ug/L (Kryptor PCT, Brahms, Hennigsdorf, Germany). The coefficient of variation of the assay at 0.1 ug/L, 0.25 ug/L, 0.5 ug/L and 10 ug/L were 16%, 7%, 5% and 3%, respectively. The test is performed at the central lab of each participating hospital. The assay time for PCT measurements require less than 20 minutes and PCT results are routinely available within one hour upon ordering.

PCT levels are communicated by the password secured website to the treating physician together with a treatment recommendation for antibiotics based on the PCT algorithm exclusively for patients randomized to the PCT intervention arm. Similarly, for the patients in the guideline-enforced group treatment recommendation based on guidelines are displayed. All participating physicians received detailed information about the use of PCT cut off ranges and the algorithm as presented in figure 2 is published in the investigators brochure and on the internet platform.

**Figure 2 F2:**
[figure not shown]
Antibiotic stewardship based on procalcitonin (PCT) cut-off ranges. Re-evaluation of the clinical status and measurement of serum PCT levels is mandatory after 6–24 h in all persistently sick and hospitalized patients in who antibiotic are withheld. The PCT algorithm can be overruled by pre-specified criteria, e.g. in patients with immediately life-threatening disease. If the algorithm is overruled and antibiotics are given, an early discontinuation of antibiotic therapy after 3, 5 or 7 days is more or less endorsed based on PCT levels. In hospitalized patients with ongoing antibiotic therapy PCT levels are reassessed on days 3, 5 and 7 and antibiotics will be discontinued using the PCT cut-offs defined above. In all patients with a very high PCT value on admission (e.g., >10 μg/L), discontinuation of antibiotic is already encouraged if levels decreased below 80 to 90% of the initial value. In patients discharged and, thus, likely uncomplicated resolution of the infection or in patients transferred to an institution not taking part in this trial the recommended total duration of antibiotic therapy is based on the last PCT level and is as following: >1 ug/L 7 days, 0.5–0.99 ug/L 5 days, 0.25–0.49 ug/L 3 days, <0.25 ug/L stop antibiotic, <0.1 ug/L STOP antibiotic. *PCT *denotes procalcitonin, *AB *antibiotics,*Tbc *tuberculosis, *ICU *intensive care unit,

In both groups, hospitalized patients are clinically reassessed and blood is sampled on days 3, 5, 7, and on the day of discharge to assess the resolution of the presumed infection. In both groups, a switch of antibiotics from intravenous to oral is advised if patients show stable or improving vital signs, resolution of the predominant clinical sign or if oral intake is possible (adequate consciousness and reflexes to swallow fluids and tablets, no malabsorption) [16,17]. In hospitalized patients with an acute bronchitis, a chest X-ray after 3–5 days is routinely performed to confirm the diagnosis and exclude pneumonia.

In all hospitalized patients hospital discharge should be considered if oral intake is feasible, vital signs are stable > 24 h (as defined above), and no evidence of acute serious co-morbidity that necessitates hospitalization is present and, if the patient has achieved pre-admission mobility state [16,17]. At the day of discharge, all patients receive 2 leaflets providing general information for the patient and the general physician (GP) regarding this trial.

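### The Figure 2 caption, as worded, encourages stopping antibiotics after a PCT fall of only 10–20% when a fall of 80–90% was probably meant

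*Protocol article*

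**What the plan says.** The rule is in the Intervention section of the protocol article, in the caption to Figure 2, which sets out the PCT algorithm for the experimental arm.

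- For hospitalized patients still on antibiotics, the general rule uses absolute levels: "PCT levels are reassessed on days 3, 5 and 7 and antibiotics will be discontinued using the PCT cut-offs defined above". Those cut-offs are in the figure, which is not available here.
- A relative rule is then added for one group, introduced by "In all patients with a very high PCT value on admission" with above 10 µg/L as the example: "discontinuation of antibiotic is already encouraged if levels decreased below 80 to 90% of the initial value".
- For patients discharged, or transferred to an institution outside the trial, the total duration of therapy depends on the last PCT level: ">1 ug/L 7 days, 0.5–0.99 ug/L 5 days, 0.25–0.49 ug/L 3 days, <0.25 ug/L stop antibiotic".

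The Intervention section also says how the algorithm reaches clinicians. The website sends PCT levels "together with a treatment recommendation for antibiotics based on the PCT algorithm exclusively for patients randomized to the PCT intervention arm", and "the algorithm as presented in figure 2 is published in the investigators brochure and on the internet platform". For the assay it reports: "The coefficient of variation of the assay at 0.1 ug/L, 0.25 ug/L, 0.5 ug/L and 10 ug/L were 16%, 7%, 5% and 3%, respectively".

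**The concern.** A level below some percentage of the initial value describes what remains, not how far the level has fallen. Under the caption's wording, a patient with a very high admission PCT meets the trigger while most of the marker is still present. A rule that asks for a fall of 80–90% is a different rule, with a far lower permitted level.

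The word *already* in the sentence shows that a trigger earlier than the absolute cut-offs is intended. Being above those cut-offs is therefore not the fault. The fault is the size of the relative threshold as written.

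This is a treatment-stopping number in the experimental intervention, and it applies to the patients with the highest PCT. Stopping rules bear on antibiotic exposure (a secondary endpoint), and the primary endpoint includes recurrence needing antibiotics and death. The Discussion also hopes that the protocol will help others implement the algorithm more widely. A reader or site working from the caption would apply a rule that is probably not the intended one.

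**Working it through.** The threshold is stated, not derived from other figures, so there is no calculation in the plan to reproduce. The check compares what the words permit with the probable alternative.

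**Inputs**
- Relative threshold: 80 to 90% of the initial value (Figure 2 caption).
- Group: very high admission PCT, for example above 10 µg/L (same caption). I use 10, 20 and 50 µg/L as illustrative admission values.
- Assay coefficient of variation (CV): 3% at 10 µg/L (Intervention section, assay paragraph).
- Only stop level visible in the caption: "<0.25 ug/L stop antibiotic", from the discharge and transfer schedule.

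**Step 1. Permitted remaining level**
- As written: remaining level < *x* × admission value, with *x* = 0.80 to 0.90. The fall needed is just over 1 − *x*, that is 10–20%.
- Read as a decrease *by* 80–90%: remaining level = (1 − *x*) × admission value, that is 10–20% of it.

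| Admission PCT (µg/L) | As written, remaining (µg/L) | Decrease *by*, remaining (µg/L) |
|---|---|---|
| 10 | 8–9 | 1–2 |
| 20 | 16–18 | 2–4 |
| 50 | 40–45 | 5–10 |

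**Step 2. Ratio of the two readings**
- At 80%: 80 / 20 = 4.
- At 90%: 90 / 10 = 9.

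The wording allows a level 4 to 9 times higher, whatever the admission value.

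**Step 3. Scale against the visible stop level (admission 10 µg/L)**
- As written: 8 / 0.25 = 32 and 9 / 0.25 = 36 times that level.
- Decrease *by*: 1 / 0.25 = 4 and 2 / 0.25 = 8 times.

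This gives scale only. Both readings lie above the stop level, as an early trigger should.

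**Step 4. Scale against assay noise**
- Assume normal errors, two independent measurements, a 3% CV for both, and analytical variation only.
- 95% limit for a change due to the assay alone: 1.96 × √2 × 3% = 8.3%.
- Required falls as written: 10 / 8.3 = 1.2 and 20 / 8.3 = 2.4 times this limit.

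The trigger as written does need a real fall, but at its lax end one only slightly larger than the assay can resolve.

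**Step 5. Search for a correction**
No other visible sentence in the article restates the rule, either as a fall of 80–90% or as 10–20% remaining.

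**The case against.** The strongest reply is that the supposed meaning has no source in the document. Nothing in the article mentions a fall of 80–90%, so the 4- to 9-fold gap depends on an inferred reading. That is correct. What the text alone establishes is what the words permit; that *by* was meant is a judgement of plausibility.

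It can also be said that the discharge schedule does not help to choose between the readings. That stands too. For an admission value above 10 µg/L, even a 90% fall leaves more than 1 µg/L, so both readings encourage stopping at levels for which the schedule gives seven days. The schedule also covers discharged or transferred patients, whereas the relative rule follows the sentence on inpatients. The conclusion here does not rest on it.

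The noise comparison does not show the rule to be wrong either, since the trigger as written exceeds the 8.3% limit. It shows only how small a fall would suffice.

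Lastly, the working algorithm is out of sight. Physicians received recommendations through the website and detailed information on the cut-off ranges, and the figure, brochure and website may all be correct. The rule only encourages stopping, the algorithm can be overruled on pre-specified grounds, and overruling must be reported to the study centre. The share of patients above 10 µg/L is not given. All this limits the claim to the caption wording and rules out any statement that patients were affected. It does not make the wording right: the sentence is intact and grammatical, and it states a specific number.

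**Conclusion.** The concern holds, for the caption wording only. As written, stopping is encouraged once PCT has fallen by just over 10–20%, leaving up to 8–9 µg/L from 10 or 40–45 µg/L from 50. The probable rule, a fall by 80–90%, would leave 1–2 or 5–10 µg/L. The difference is 4- to 9-fold.

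The arithmetic needs no assumption beyond the plain meaning of the words. That the authors meant *by* is an inference. The assay-noise figure also assumes that the 3% CV at 10 µg/L applies to both measurements and ignores biological variation. No harm is demonstrated, and sample size, non-inferiority margin and type I error are unaffected. Because this is a numerical stopping threshold in the experimental algorithm, it should be fixed rather than left as a stylistic point.

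**What to change.** 1. Ask the clinical leads to confirm what was meant.
2. If it was a fall of 80–90%, reword the sentence so that discontinuation is encouraged once levels have decreased *by* 80 to 90% of the initial value (i.e. to 10–20% of it). If the literal meaning was intended, state explicitly that a fall of 10–20% is enough.
3. Check that Figure 2, the investigators' brochure and the website carry the same rule.

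Two optional clarifications, neither part of the fault: give one cut-off in place of a range, and add a clause saying that the duration schedule based on the last value takes over at discharge or transfer.

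The cost is one word and a short parenthesis in one caption sentence, plus the check of the three other places. Nothing in the design or analysis changes.

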### Outcomes and adverse events

The primary endpoint of this trial is the combined disease-specific failure rate within 30 days. The following events are considered as failures: (**a**) radiologically, microbiologically or clinically confirmed recurrence of infection in need of antibiotics, (**b**) local or systemic complications from LRTI including persistence or development of pneumonia (including nosocomial), parapneumonic effusions, lung abscess, empyema, any abscess (pharyngeal, parapharyngeal, sinusitis requiring sinus drainage, any remote abscess), acute respiratory distress syndrome (ARDS), (**c**) admission to the intensive care unit (ICU), (**d**) disease related hospital readmission and (**e**) death from any cause.

The secondary endpoints of this trial are (**a**) antibiotic exposure for LRTIs (antibiotic prescription times duration of antibiotic therapy), (**b**) side-effects from antibiotic treatment, (**c**) time to clinical stability, (**d**) length of hospital stay and (**e**) quality of life according to EuroQol and LRTI-specific disease activity score[22]. Five projects performed alongside to this trial (cost-effectiveness of PCT guided antibiotic therapy, impact of nursing and social factors for rate and duration of hospitalization, other biomarkers as diagnostic and prognostic tools in LRTI, free cortisol and copeptin levels to assess disease-related stress, microcalorimetry as a novel method for rapid diagnosis of bloodstream infections) synergize scientific efforts.

Outcomes are assessed during hospital stay at days 3, 5 and 7, and at hospital discharge and by structured phone interviews at days 30 and 180 (figure 1) by medical students blinded to the treatment allocation of the patients. In case the patient is indicating the prescription of any new antibiotic or any unnamed drug following hospital discharge or is unable to give adequate information, or has been rehospitalised, the interviewer is obliged to contact the treating GP or the hospital and to receive notification of the prescription or a copy of the hospital transferral or demission letter.

Endpoints are reassessed by an independent endpoint committee of at least 2 clinicians blinded to patient allocation. Endpoint judgment is based on the case report form and, if necessary, on hard copies of the hospital chart that are made anonymous and blinded in regard to any information on PCT. In order to truly blind endpoint assessors all information on PCT will be discarded on relevant documents.

An adverse event in a subject is defined as any occurrence of unfavourable and unintended clinically relevant medical sign, symptom, or disease temporally associated with the study which does not necessarily have a causal relationship with the study procedure. If an adverse event occurs, the responsible clinician involved in the case is contacted by an unblinded member of the study team to verify all information and to complete a serious adverse event form. All adverse events within 180 days after study inclusion are monitored and continuously evaluated by the data safety and monitoring board. All adverse events must be followed until resolution, until the condition stabilizes, until the event is otherwise explained, or the subject is lost to follow-up or has died.

